## Method

### Participants and power analysis

The target group are elite, sub-elite, and recreational athletes from four sports (curling, volleyball, i.e., indoor and beach, tennis, and hockey, i.e., floorball and ice hockey). We chose these sports because they are suited to sample comparable short sequences (see primary outcome below) within a game or a competition, as opposed to, for example, soccer. Athletes who are members of the respective Swiss national sport associations will be contacted and offered the opportunity to participate. Criteria for exclusion are a likely mental disorder, significant previous experience with PST or MI, less than 4 h of athletic training per week, or being younger than 18.

The sample size calculation is based on differences between the waiting-list control group (WC) and one of the treatment groups (PST or MI) after the intervention. Based on previous research, we assume medium effect sizes of d = .6 [39]. Testing one-sided, given that α = .05 and a power of 80 %, we would need 108 participants (36 for each group) to be able to detect the effect.

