### Study objectives and hypotheses

The primary objective of this study is to assess the effects of PST and MI in promoting FAB in elite athletes. We hypothesize that both active interventions are more effective than a waiting-list control condition in promoting FAB. We do not expect PST to be superior over MI or vice versa; rather, they are expected to increase FAB through different routes.

Thus, the secondary objective is to examine potential factors that mediate the effects of PST and MI. We assume that the effect of PST on FAB is mediated by the use of psychological skills (the manipulation check of the PST intervention) and the experienced ability to control one’s thoughts and emotions. We expect the effect of MI on FAB to be mediated by participants’ self-rated mindfulness (the manipulation check of the MI intervention) and acceptance of/defusion from unpleasant experiences. Finally, we hypothesize the effects of both PST and MI on FAB to be mediated by general level of attention and perceived attention control in games or competitions.

A third objective is to examine potential moderators of the effects of PST and MI. We assume that the more athletes interpret their current experience as something that has to be regulated, the more they profit from regulation or coping strategies being utilized/taught in PST and MI. We therefore hypothesize that athletes high in ego orientation or those with low values of self-esteem and self-compassion benefit the most from PST and MI. Such athletes might perceive performance situations as threatening for their psychological needs to a greater chance [24, 28], especially when the athletic task at hand is difficult or the competition is perceived as important. Perceived threat might lead to, for example, more competition anxiety, negative outcome expectations, or cognitive interference. In addition, we aim to investigate the role of treatment expectancies (common factor) and treatment adherence for improvements in FAB.

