### Study design and group allocation

Figure 1 shows an overview of the procedure (parallel group design). After a first contact and checking for inclusion and exclusion criteria (time 0), athletes will be stratified for gender, sport, and performance level, then randomly assigned to either the PST group, the MI group, or the WC group, and will be informed about their experimental condition. Members of the same team (i.e., curling, volleyball, or hockey) will be assigned to the same intervention group. For randomization, a computer-generated random-number sequence will be prepared in advance and sealed in opaque, consecutively numbered envelopes by an independent researcher. An independent researcher will open the envelopes in sequence based on client number, to determine the participant’s assignment to the groups.

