### Statistical analysis

All analyses will be conducted as intent-to-treat. To assess if randomization is successful in balancing demographic characteristics across the treatment groups, we will compare age, use of psychological skills, mindfulness, and performance level using Student’s t-tests. Two-way (group x time) repeated measures ANOVAs will be used to answer the question regarding whether the intervention (independent variable) had an effect on the primary and secondary outcome measures (dependent variables). Significant overall effects will be followed up with post hoc tests and contrasts between intervention programs (e.g., PST and MI together compared to the WC group). Significance levels will be set at *p* = .05. If there are significant differences between different intervention sub-groups, we will perform multilevel analyses. To test the mediation and moderation models, we will follow the requirements for mediation and moderation suggested by Hayes [36]. The first three authors of this manuscript will have access to the full dataset.

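### The stated 80% power belongs to a one-sided test of a single contrast in independent athletes, not to the group x time F test planned in clustered athletes

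*Protocol article*

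**What the plan says.** In the protocol article, Participants and power analysis, the calculation rests on "differences between the waiting-list control group (WC) and one of the treatment groups (PST or MI) after the intervention". Its other inputs are "we assume medium effect sizes of d = .6" and "Testing one-sided, given that α = .05 and a power of 80" per cent. The result is that "we would need 108 participants (36 for each group) to be able to detect the effect". That section mentions no pre-post correlation, intracluster correlation or design effect.

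Three other sections bear on what that power should describe:

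- Study objectives and hypotheses: "We hypothesize that both active interventions are more effective than a waiting-list control condition in promoting FAB".
- Statistical analysis: "Two-way (group x time) repeated measures ANOVAs will be used to answer the question" of an intervention effect, at a significance level of .05. Then "Significant overall effects will be followed up with post hoc tests and contrasts between intervention programs"; the example given is PST and MI pooled against waiting list. Multilevel models are used only if sub-groups differ significantly.
- Study design and group allocation: "Members of the same team (i.e., curling, volleyball, or hockey) will be assigned to the same intervention group". The description of the interventions adds delivery in groups of six, six groups per condition.

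**The concern.** The power section and the analysis section describe different tests. A three-group F test has no direction, so the gain from one-sided testing used in the sizing is not available to it. A contrast reached only through a significant F cannot have more power than the same contrast tested directly. Team allocation and group delivery make athletes in a cluster more alike, which reduces the information in 36 athletes per arm.

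The one follow-up contrast named, both interventions pooled against waiting list, cannot show that each intervention works. If one has d = 0.6 and the other 0, the pooled difference is 0.3 and the contrast is still significant in 31% of trials (two-sided, 72 against 36).

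The stake is how the result is read. A non-significant result would be judged against an 80% figure that the planned analysis has not been shown to have.

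**Working it through.** **Inputs from the article:** d = 0.6 (SD 1), 36 per arm, three arms, α = .05. **Assumptions, not in the article:** pre-post correlation r, ICC, and clusters of six in every arm.

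**1. The article's own figure.** Two-sample t-test, one-sided .05, 80% power: n = 35.04 per arm, taken to 36, and 3 × 36 = 108. At 36 the noncentrality is 0.6 × √(36/2) = 2.546 on 70 df, and power is 80.9%. The figure reproduces with no allowance for anything else.

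**2. The same contrast, two-sided.** Same noncentrality, critical value at .975: power 70.9%. For 80%, n = 44.6, so 45 per arm.

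**3. The planned F.** Waiting-list athletes are assessed only before and after the intervention, so the three-group comparison has two time points. The interaction F is then a one-way ANOVA on change scores. With means 0, 0.6, 0.6 (grand mean 0.4), the squared deviations sum to 0.16 + 0.04 + 0.04 = 0.24. The change-score variance is 2(1 − r), so

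λ = 36 × 0.24 / [2(1 − r)] = 8.64 / [2(1 − r)], on F(2, 105).

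At r = .5 the divisor is 1 and the result equals a comparison of post scores. Clustering divides λ by 1 + (6 − 1) × ICC, which is 1.25 at ICC .05; here the ICC is that of the change score.

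| r | F, independent athletes | F, assumed ICC .05 |
|---|---|---|
| .3 | 58% | 49% |
| .5 | 74% | 64% |
| .6 | 83.5% | 74% |
| .7 | 93% | 86% |

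**4. Contrasts on post scores, independent athletes (simulation where joint or gated).**

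| Criterion | One-sided | Two-sided |
|---|---|---|
| One contrast, no gate | 81% | 71% |
| One contrast, after a significant F | about 70% | 65% |
| Both contrasts, no gate | 70% | 57% |

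Reading the follow-up contrasts as one-sided therefore does not recover 80% on these inputs: the gate alone removes about 11 points.

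**5. Clustering applied to single contrasts.** Noncentrality 0.6 × √(18 / design effect), keeping 70 df:

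| Assumed ICC | Design effect | One-sided | Two-sided |
|---|---|---|---|
| .02 | 1.10 | 78% | 67% |
| .05 | 1.25 | 73% | 61% |
| .10 | 1.50 | 66% | 54% |

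If only the active arm is clustered, the average design effect is (1 + 1.25)/2 = 1.125 at ICC .05 and (1 + 1.50)/2 = 1.25 at ICC .10. Power is then 77% and 73% one-sided, 66% and 61% two-sided.

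These losses apply to an analysis that respects the clusters. An F test that ignores them pays in false positives instead: in simulation it rejects about 9% of the time at ICC .05 and 13.5% at ICC .10, against a nominal 5%.

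**The case against.** The strongest reply is that nothing has been miscalculated. The article states its contrast, sidedness, α and d openly, and 36 per arm follows from them. That stands: this is a mismatch between two sections, not an arithmetic slip.

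A reader might go further and infer that the trial is underpowered, with a known and substantial chance of missing d = 0.6. The documents do not support that. The planned test uses baseline values, and its power turns on r. With independent athletes, r = .6 gives the F 83.5% and a two-sided contrast on change scores 80%. With ICC .05 and clusters of six, the F reaches about 80% at r = .65. Equally, r below .5 would make matters worse. Because r is not given, the supportable statement is that 80% has not been demonstrated. The sizing itself refers to differences after the intervention and claims no gain from baseline.

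The clustering figures are also conditional. Waiting-list athletes have no treatment group until after the second assessment, and tennis is not among the sports allocated by team, so the loss may be smaller; teams larger than six would make it larger.

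A reader might also take the hypothesis as a rule that both contrasts must succeed. It can equally be read as two separate hypotheses, for which power per contrast is usual; the 70% and 57% joint figures apply only under the stricter reading. Finally, the pooled contrast is offered as an example, and the post hoc tests in the same sentence can include the pairwise comparisons.

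What remains is that the article states both the sizing test and the analysis test, and they differ. That is not detail left to a fuller document.

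**Conclusion.** The point holds as a mismatch between the power statement and the analysis, and it should be fixed. The 80% describes a one-sided t-test of one contrast in independent athletes. On the same inputs, using post scores (equivalently, change scores at r = .5) and no clustering, the planned F has 74%, one two-sided contrast 71%, and one contrast behind the F about 70% one-sided or 65% two-sided.

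These shortfalls do not depend on any ICC. Clustering lowers them further by an amount that rests on assumed ICCs. A pre-post correlation of about .6 or more without clustering, or slightly above .65 at ICC .05, would bring the F itself back to 80%, but the article neither states nor relies on one.

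**What to change.** Keep 108 athletes and change the wording of the two sections.

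- Use the same sidedness in the power and analysis sections.
- Name PST versus waiting list and MI versus waiting list after the intervention as the two contrasts that answer the primary hypothesis. Keep the pooled contrast as supportive.
- Restate power for the test actually planned, with r and ICC as explicit assumptions over a range. For example: about 71% per two-sided contrast on post scores before clustering, 61% at ICC .05 and 54% at ICC .10 with clusters of six in every arm. If the analysis stays on group x time, give the figures by r as in the table above.
- If contrasts remain conditional on the F, quote the power with that condition included.
- If the claim is that both interventions work, also give the power to show both: about 70% one-sided or 57% two-sided on post scores, before clustering and without the F condition.

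The cost is some rewording and a less favourable stated power; no additional recruitment is implied.

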### Description of the PST and MI intervention

The PST intervention will be adapted from PST programs like Ebersbächer’s *Mental Training* [15]. It involves the practice of four psychological skills (self-talk, imagery, goal-setting, and arousal control) and will be based on the latest guidelines and recommendations about instruction and application of these skills [1, 27, 73, 77]. A sport psychologist trained in specialized PST interventions will explain the expected sport-specific benefits to the participating athletes and advise athletes to do homework between group sessions.

The MI will be adapted from mindfulness-intervention programs, including Mindfulness-Acceptance-Commitment (MAC) [25], Acceptance and Commitment Therapy (ACT) [38], and Mindfulness-Based Stress Reduction (MBSR) [45]. A sport psychologist trained in specialized mindfulness-based interventions will explain the expected sport-specific benefits to the participating athletes and advise athletes to do formal and informal mindfulness practices at home between group sessions.

The interventions will be realized in groups of six athletes each, leading to six sub-groups in each condition (6 × 6 = 36 athletes, see power analysis). A manual will accompany the instructions for the interventions. All components of both interventions must be administered according to the manual’s specifications. Two independent raters will evaluate the adherence to each intervention on the basis of video recordings. In addition to psycho-education and practice at home guided by audio files that can be played on computers or portable devices such as smart phones. All participants will also be provided with a calendar of their exercises to tick off as they are completed, and daily text messages will remind them to practice their PST or mindfulness exercises. Each intervention consists of four 2-h sessions over the course of 5 weeks. Participants will be advised to practice daily and record their amount of practice. All sessions will conducted at the center for elite sports of the Swiss Federal Institute of Sport.

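### The 36 athletes per arm required by the power calculation are also the 36 per arm planned for intake, so the stated 80% power holds only if post-intervention outcome data are essentially complete

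*Protocol article*

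**What the plan says.** In the Protocol article, under Participants and power analysis, the sample size is "based on differences between the waiting-list control group (WC) and one of the treatment groups (PST or MI) after the intervention". The inputs are "Testing one-sided, given that α = .05 and a power of 80" per cent, and "we assume medium effect sizes of d = .6". The result is that "we would need 108 participants (36 for each group) to be able to detect the effect".

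Under Description of the PST and MI intervention, the sessions are planned as follows: "The interventions will be realized in groups of six athletes each", "leading to six sub-groups in each condition (6 × 6 = 36 athletes, see power analysis"). The size of each condition is thus tied by cross-reference to the number from the power analysis.

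Under Study design and group allocation, athletes are randomised after screening (T0), before the pre-intervention assessment (T1). The post-intervention assessment (T2) follows a five-week programme, and the primary outcome, functional athletic behaviour (FAB), is rated during an actual game or match. Under Statistical analysis, all analyses are to follow intent-to-treat. The article text names no expected loss, over-recruitment or replacement of athletes.

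**The concern.** A sample size derived for a comparison after the intervention counts athletes who supply a value at that time. If the number taken in equals that count, the stated power is reached only when practically nobody is lost between randomisation and the T2 match. An athlete may leave the programme, be injured, or not play a match that can be assessed. Team-mates share an arm, so one team missing its match could remove several values from one arm together.

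At stake is the accuracy of the stated 80%. The Background faults earlier trials for having too few subjects to detect effects, so readers are likely to take this trial's power figure as a strength. The figure should describe the number expected in the analysis.

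**Working it through.** **Inputs** (Participants and power analysis): one-sided α = .05, power 80%, d = .6, two independent groups compared after the intervention, 36 per group. Planned size per condition (Description of the PST and MI intervention): 6 × 6 = 36.

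**Formula.** For a one-sided two-sample t-test with n₁ and n₂ athletes analysed:

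- degrees of freedom: n₁ + n₂ − 2
- noncentrality: d × √(n₁n₂ / (n₁ + n₂))
- power: probability that a noncentral t variable with these parameters exceeds the 95th percentile of the central t distribution

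**Step 1: the plan's own figure.** With 36 and 36, the degrees of freedom are 70, the noncentrality is .6 × √(1296/72) = .6 × √18 = 2.546, the critical value is 1.667 and power is 80.95%. With 35 and 35, power is 79.96%. So 36 is the smallest equal group size that reaches 80%, and the stated figure reproduces. The normal approximation gives 35 per group, and a two-sided t-test would need 45, so the stated 36 is the one-sided t-test result.

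**Step 2: how many losses the 80% tolerates.**

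| Analysed in the two compared arms | Athletes lost in total | Power |
|---|---|---|
| 36 and 36 | 0 | 80.95% |
| 36 and 35 | 1 | 80.45% |
| 35 and 35 | 2 | 79.96% |
| 36 and 34 | 2 | 79.93% |

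The second loss, whether from one arm or one from each, takes power below 80%, by 0.04 or 0.07 percentage points.

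**Step 3: larger losses.** The article gives no rate, so the rates below are assumptions, applied equally to both compared arms and rounded down to whole athletes remaining.

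| Assumed loss per arm | 36 × (1 − loss) | Analysed per arm | Power at d = .6 | d detectable with 80% power |
|---|---|---|---|---|
| 5% | 34.2 | 34 | 78.9% | .61 |
| 10% | 32.4 | 32 | 76.7% | .63 |
| 15% | 30.6 | 30 | 74.3% | .65 |
| 20% | 28.8 | 28 | 71.6% | .67 |

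The last column solves the same power formula for d at 80%.

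**Scope.** The powered comparison uses T2 only, so a missing T1 match does not enter these figures. All of them treat athletes as independent, as the calculation does.

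**The case against.** The strongest reply is that nothing in the power analysis is wrong. The arithmetic is right, and a condensed article may leave expected loss, over-recruitment and replacement to the full protocol, which is not shown. The flow figure is not shown either and could carry recruitment numbers. The groups of six describe how sessions are organised, and no sentence caps recruitment or rules out replacing athletes. This stands in part: the absence of a loss rate alone would be no finding. What remains is that the article does give a size per condition and justifies it by the power analysis, and that link is sound only with near-complete data.

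A second reply is that the shortfall at the threshold is negligible. That is correct. A reader might infer that power collapses after two losses; in fact it falls by about one percentage point, from 80.95% to just under 80%. Only assumed losses of the order of 10% or more make a visible difference.

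A third reply is that the trial plans a group × time repeated-measures ANOVA and assigns team-mates together, so a restated t-test power is not the power of the planned analysis. That is also correct. Use of the baseline and clustering can move power in opposite directions, by amounts the article does not allow one to compute. Any restated figure must carry that limit.

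A reader might also infer that a non-significant result will be over-interpreted. The article contains no rule that uses the 80% to read such a result, so this is a possibility and not something the plan states.

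Intent-to-treat does not answer the point. It keeps athletes in their assigned arm but does not supply outcomes that were never observed.

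**Conclusion.** The point holds in a limited form. The 36 per group is the exact minimum for the calculation's own test, and the article sets the size of each condition at that same 36. The stated 80% therefore requires that no more than one athlete across the two compared arms lacks a T2 value. The cost is small for a few losses and moderate for larger ones: about 79%, 77%, 74% and 72% power at assumed losses of 5%, 10%, 15% and 20% per arm. These figures rest on the assumed rates, equal loss in both arms, independent athletes and the one-sided post-intervention t-test.

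Two stronger conclusions are not supported. The sample size calculation is not in error, because it reproduces exactly. Nor do the documents show that the trial will be underpowered, because they give no loss rate and the planned analysis is a different one.

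**What to change.** Keep 108 athletes. Under Participants and power analysis:

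- say that 108 is the number randomised and that 80% power assumes complete T2 data;
- give the expected proportion without a T2 FAB value;
- restate the power, or the detectable d, for the number then analysed. At 10% to 20% loss, for example, 32 to 28 per arm are analysed, with power of about 77% to 72% at d = .6, or a detectable d of about .63 to .67;
- note that this applies to the one-sided, independent, post-intervention t-test used in the calculation, and not to the group × time ANOVA or to clustering by team.

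Under Description of the PST and MI intervention, align the wording so that 36 per condition is described as the number allocated and is not presented as meeting the power requirement regardless of loss.

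The cost is a few sentences of text and a slightly less favourable stated power. No extra athletes and no change to the design or analysis are needed.

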### Study design and group allocation

Figure 1 shows an overview of the procedure (parallel group design). After a first contact and checking for inclusion and exclusion criteria (time 0), athletes will be stratified for gender, sport, and performance level, then randomly assigned to either the PST group, the MI group, or the WC group, and will be informed about their experimental condition. Members of the same team (i.e., curling, volleyball, or hockey) will be assigned to the same intervention group. For randomization, a computer-generated random-number sequence will be prepared in advance and sealed in opaque, consecutively numbered envelopes by an independent researcher. An independent researcher will open the envelopes in sequence based on client number, to determine the participant’s assignment to the groups.

